### Measures

A summary of measures is included in Table 2.

**Table 2 Tab2:** Summary and timeline of outcome measures for intervention and comparison communities

Measure/ variable	Target audience	Tool	Year 1	Year 2 (PRE)	Year 3	Year 4	Year 5 (POST)
Coalition self-assessments	Community coalition members			x	x	x	x
Parental perceptions and practices	Low-income parents of preschool age children living in project communities	Active Where [17]		x			x
Community-at-large environment	Project communities	CHLI [18]		x			x
Neighborhood environment	Project community neighborhoods	CHLI [18]		x			x
Early Childhood Center policies and practices	Project community early childhood centers	CHLI [18]		x			x
Project Reflections	Project staff, coaches			x	x	x	x
Interviews	Coalition members, coaches						x
Ripple effect mapping	Community coalition members						x

*CHLI* Community Healthy Living Index

### Coalition Self-Assessment Survey (CSAS)

The CSAS will be used to assess coalition development, functioning and effectiveness. It contains six different domains of measurement: Environmental Characteristics (of the coalition), Structural Characteristics (of the coalition), Functional Characteristics (of the coalition), Coalition Programs and Interventions, Intermediate Measures of Coalition Effectiveness, and Outcome Measures of Coalition Effectiveness. This tool will be administered annually to each of the states’ community health coalition members to serve as an evaluative measure for assessing function, process, and outcomes of the coalitions; and to provide quantitative information on the progress of the coalitions throughout the span of the project.

### Active where?

The Active Where? Parent Survey will be used as a quantitative assessment of parent perceptions of the built environment. This survey will be adapted, with permission, from the Active Where? Parent-child Survey [17] to contain a demographic section and 11 sections to assess home and neighborhood environment characteristics including: recreation and sports facilities where your child plays; barriers to activity in the neighborhood; access to services; neighborhood streets; places for walking/biking; neighborhood surroundings; neighborhood safety; local environment; physical activity; rules for eating; and food. Questionnaire sections with Cronbach α < .70 will be examined for low scoring items and, items will be deleted to improve reliability. Content and face validity will be established by the project research team.

A total of 30 participants will be recruited from each of the rural, low-income target intervention (*n* = 7) and comparison communities (*n* = 7) to complete the Active Where? questionnaire. Active Where? will be administered at baseline and in the final year of the project. Eligibility criteria for each participant will include: being at least 18 years of age and a parent or legal guardian of a child between the ages of 3 and 5 years, ability to speak and/or read English, being a resident of the target community, and being enrolled or having a child enrolled in programs such as Head Start, SNAP (Supplemental Nutrition Assistance Program) or WIC (Special Supplemental Nutrition Program for Women, Infants and Children). The interviewer will read the consent form or information sheet to the participants and allow them to ask questions before beginning the survey interview. Using a standard protocol, questionnaires will be administered face-to-face at the site of recruitment and each parent participant will complete the survey once. It is estimated that each interview will take approximately 45–60 min. Participants will be given a small monetary incentive after completing the interview.

### Community Healthy Living Index (CHLI)

The YMCA’s Community Healthy Living Index (CHLI) assessments will be used in each of the project communities [18]. The CHLI contains assessments for six key community settings: afterschool child care sites, early childhood programs, neighborhoods, schools, work sites, and the community at large. Each assessment contains questions about policies and practices that support healthy lifestyles. Three of the six assessments will be selected (early childhood programs, neighborhood and community at large) for the project as they specifically support the project objectives. Assessments will be conducted by at least one individual in the community health coalition at baseline, and follow-up assessments will be conducted in the final year of the project. During the first year of data collection, communities will utilize the results of the CHLI tools to identify areas that need improvement within the various settings and plan for action to improve the ecological environment of their community to ultimately prevent childhood obesity.

### Qualitative data

Throughout the project, each state’s co-investigator, graduate student and community coach will complete monthly or quarterly reflections to capture progress, impressions and potential changes over the course of the research. At the end of the project, community coalition member and coach one-on-one interviews will provide additional focused qualitative information. Reporting on qualitative data collection will adhere to the consolidated criteria for reporting qualitative studies (COREQ) guidelines [19].

To assess the value of the menu of evidence-based or evidence informed educational programs, interviews will be conducted with coalition members of both the intervention and control communities. The interviews will be conducted by trained staff, recorded and transcribed for analysis. Participants will be asked their opinions about the usefulness and quality of the items in the menu of intervention strategies that were provided to them.

### Ripple effect mapping

Ripple effect mapping (REM) is a mind mapping technique used to examine how establishing natural and built assets can serve as a catalyst to leverage other community assets. REM is a promising way of measuring impact that engages stakeholders and program participants. Hanson and Kollock state, “REM is best conducted for in-depth program interventions or collaborations that are expected to produce broad or deep changes in a group, organization, or community” [20]. The emergence of new organizations, institutions, programs, policies, or strategies related to the intervention will be studied. The emergent support of organizations and institutions to sustain interventions as a broader community development “spiraling up” will be noted [21]. REM will be used in both intervention and comparison communities using a standard protocol and specialized mind mapping software [22]. A research team from each state will conduct ripple effect mapping with the two community coalitions in their state after the coalitions complete their final interventions.

### Statistical analysis

Objectives 1–5 are project development or process objectives which will be evaluated using monthly or annual reports from each state during the five year project. Objective 6 (perceived value of the menu of evidence-based obesity prevention resources) will be evaluated by qualitative data analysis techniques specifically, interviews with community coalition members. The main project objective, objective 7 (enhancement of community capacity to prevent childhood obesity by Community Coaching) will be evaluated using a mixed-methods data analysis approach with data from several of the project instruments (CHLI, Active Where?, and CSAS). Descriptive statistics including frequencies and repeated measures ANOVA or corresponding non-parametric tests will be conducted to detect changes between intervention and comparison communities before and after the four year intervention for quantitative data related to policy, systems and environmental change variables using SAS 9.4 software (SAS Institute Inc.). Significance will be set at *P* < .05.

Qualitative data (reflections and interviews) will be analyzed using the classic analysis approach [23] including constant comparison analysis to generate themes and search for text that inform those themes. Ripple effect mapping will be analyzed through content analysis by categorizing identified community activities and changes into the different levels of the social-ecological model. Dominant emergent themes from the qualitative data will be weaved together with quantitative data to develop a theoretical model representing how communities were impacted by the project.

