## Methods

### Study design

The focus of this project is to improve understanding of those factors necessary to mobilize communities to make policy, system or environmental changes aimed at the prevention of childhood obesity within seven North Central U.S. States (IN, KS, MI, ND, OH, SD, WI). Using a quasi-experimental design, the research will examine how building community capacity with a community coaching model in rural, low-income communities contributes to the communities’ increased ability to prevent childhood obesity. The Ecological Model of Childhood Overweight will serve as the foundation for reviewing characteristics that could affect a child’s weight status in relation to the multiple environments surrounding that child [8].

Low-income, rural communities will be recruited to apply for the project from each of the seven participating states. Rural areas will be defined based on the Office of Management and Budget’s definition, which delineates an area as rural if there is no presence of a metropolitan statistical area or a core urban area with a population of 50,000 or more [16]. Low-income will be defined based on the community’s average income rate being below the state’s average poverty rate. Other criteria will include that the community has an existing community health coalition and community focus to tackle childhood obesity prevention. Similar-size intervention and comparison communities will be selected from each state. Once selected through an application screening process to ensure that selection criteria are met, communities will be randomly assigned to the intervention or comparison group. Each state will have one intervention and one comparison community. The project sample size (*n* = 14) will be sufficient to detect large effect sizes (d ≥ 0.8) with 95 % power for a two-tailed test at alpha = .05 between intervention and comparison communities from pre to post using the community as the main unit of measure and community level variables as the main outcomes.

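### The main hypothesis (objective 7) has no primary outcome, and no rule says which of an unstated number of tests at P < .05 would support it

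*Protocol article*

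**What the plan says.** The objectives listed at the end of the Background section contain one main hypothesis, under objective 7: that coaching enhances community capacity. The Statistical analysis section calls this the main project objective and evaluates it by mixed methods with "data from several of the project instruments (CHLI, Active Where?, and CSAS". The quantitative part is repeated measures ANOVA or a non-parametric counterpart, applied to variables on policy, systems and the environment, comparing coached and uncoached communities before and after the intervention. The only decision rule is "Significance will be set at *P* < .05". The abstract repeats that threshold.

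Each of the three instruments has several parts:

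- CHLI: "Three of the six assessments will be selected (early childhood programs, neighborhood and community at large".
- Active Where?: a demographic section plus "11 sections to assess home and neighborhood environment characteristics".
- CSAS: "It contains six different domains of measurement".

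The Study design section sizes the study for a "two-tailed test at alpha = .05 between intervention and comparison communities", with "community level variables as the main outcomes". It does not name those variables. The article does not rank the instruments, designate a primary outcome, or say which result or combination of results would count as support for the hypothesis.

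**The concern.** A single main hypothesis needs a single deciding result, or a stated rule for combining several. Here the deciding set is three multi-part instruments that share one unadjusted threshold. The .05 holds for each test taken singly, but the claim about coaching could rest on whichever score falls below it. The power statement has the same gap, because its stated power belongs to no identifiable variable.

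The Discussion says the findings will feed a best-practices tool kit that teaches coaching techniques to other rural communities. If one or two scores out of many differ, a reader of the results could not tell whether the hypothesis was confirmed or whether chance had supplied a candidate.

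**Working it through.** **The plan's own figures.** The article gives no family-wise error rate and no number of tests, so there is nothing of that kind to reproduce. Its one design figure is 95% power for 14 communities at d ≥ 0.8. A plain two-sample t calculation with 7 per arm does not reproduce it (about 28%). That is a separate matter, and nothing below depends on it.

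**Inputs**

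- Two-sided level per test: .05 (Study design; Statistical analysis).
- Communities: 7 per arm (Study design).
- Parts of the instruments: CHLI 3, Active Where? 11 without the demographic section, CSAS 6 (the respective Measures sections).
- Number of tests, m: not stated. Three illustrative values are used: one score per instrument, m = 3; CHLI and CSAS parts only, m = 3 + 6 = 9; all parts, m = 3 + 11 + 6 = 20.
- Correlation between scores: not stated; assumed below.

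**Step 1: independent scores, no true effect.**

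At least one significant result in either direction: 1 − 0.95^m. At least one significant result in favour of coaching: 1 − 0.975^m, since half of the two-sided .05 lies in that direction.

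| m | Either direction | In favour of coaching |
|---|---|---|
| 1 | 5% | 2.5% |
| 3 | 1 − 0.857 = 14% | 1 − 0.927 = 7% |
| 9 | 1 − 0.630 = 37% | 1 − 0.796 = 20% |
| 20 | 1 − 0.358 = 64% | 1 − 0.603 = 40% |

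These figures depend only on each test having its nominal level, not on sample size or power.

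**Step 2: correlated scores.** Scores from the same communities will probably correlate, which lowers the rates. The simulation used 40,000 runs of 7 against 7 communities, with 20 scores in blocks of 3, 11 and 6, no true effect and a two-sample t test on each score. With two time points, the group-by-time test in a repeated measures ANOVA is equivalent to this t test on change scores.

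| Assumed correlation within / between instruments | Either direction | In favour of coaching |
|---|---|---|
| 0 / 0 (check on step 1) | 64% | 40% |
| 0.3 / 0.1 | 60% | 33% |
| 0.5 / 0.2 | 52% | 28% |
| 0.7 / 0.3 | 42% | 21% |
| 0.8 / 0.8 | 24% | 12% |

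Even with very high correlation throughout, the rate is more than four times nominal (24% against 5%; 12% against 2.5%). With 9 scores and the same correlated settings, the rates run from 35% down to 18% in either direction, and from 18% down to 9% in favour of coaching.

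**The case against.** The strongest reply has three parts.

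1. *A journal article condenses the protocol, and score definitions and multiplicity rules commonly sit in an analysis plan.* This is fair for those details. It does not cover the outcome that decides the main hypothesis and anchors the sample size, which belongs in the protocol. Nor is the article silent: it states the deciding set and one threshold.

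2. *Objective 7 is judged by mixed methods, so no single P value need decide it.* The integration with qualitative themes is real and limits how far one score would be pressed. But the article also sets a significance level and a power for the comparison, so it does plan a formal test, and the test needs a named object.

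3. *The number of tests is unknown.* This stands, and it is why the size can only be given as a range.

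A reader might also infer more than the article supports:

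- *That about 20 scores will each be tested.* Twenty is a sum over the parts of the instruments. The Statistical analysis section restricts testing to variables on policy, systems and the environment and gives no count. Some Active Where? content, such as household eating rules, may fall outside that class.
- *That a false finding for coaching is likely.* The 64% counts both directions and assumes independence. In favour of coaching, the highest figure is about 40%.
- *That an isolated significant score is as likely noise as signal.* That needs a prior. At an assumed 30% power, true and false positives are equally frequent only if about .05/.35 = 14% of scores have a true effect, and the article gives no such proportion.
- *That a Bonferroni correction over 20 scores could never succeed.* The level .05/20 = .0025 is below the smallest two-sided P of an exact paired test on 7 pairs, 2/128 = .0156. But the article does not specify that test. ANOVA has no such floor, and an exact unpaired 7-against-7 test can reach 2/3432 = .0006.
- *That the CHLI community-at-large assessment is the obvious primary outcome.* The article does not say that it yields one score, and the CSAS is at least as close to capacity.

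**Conclusion.** The point holds in this form: objective 7 has no primary outcome, the main outcomes behind the sample size are unnamed, and nothing says which result supports the hypothesis. If the stated threshold is applied to each score tested and any significant score may count as support, the false-positive rate for the main claim exceeds 5% in every multi-score scenario examined. The counts of 3, 9 and 20 are illustrative, because the article fixes no number, and the correlations in step 2 are assumptions. The precise inflation is therefore unknown, but its direction is not in doubt. This should be corrected, though it does not show that a false claim for coaching is probable.

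**What to change.** The Study status section says analysis of the main outcomes has still to begin. Before it does, and before post-intervention data are examined by group, amend the analysis text, with a date, in one of two ways:

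- **Preferred:** name one community-level primary outcome for objective 7, define how its score is formed, and test it alone at two-sided .05.
- **Alternative:** define one summary score for each of CHLI, Active Where? and CSAS, and test the three in a stated fixed order, each at .05 until one fails, or with Holm adjustment, whose first step is .05/3 = .0167.

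The choice of outcome is the sponsor's. A CSAS capacity score fits the wording of the hypothesis; a CHLI score fits the environmental target. The Study design section should then name the same outcome in the power statement.

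The confirmatory claim about coaching should rest on that result. Report all remaining scores as supportive, with estimates and 95% confidence intervals and no claim of significance.

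The cost is a change of wording. The downside is that the other scores lose confirmatory status. Under the alternative, the stricter Holm steps cost some power in a study of 14 communities, and a fixed order stops at the first failure.

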The specific project objectives are:Existing health related coalitions in 14 rural U.S. communities (two per state, one as an intervention community and one as a comparison community) will be supported to improve the environment for nutrition and physical activity of 4‐year‐old children in their community.The project team will identify or develop community assessment tools and assemble them into a *Child Ecological Model Assessment Tool Kit.*The project team will create a menu of evidence‐based or evidence‐informed educational programs and protocols addressing healthy eating and physical activity for 4‐year‐old children from which communities will select.Community coalitions will create a plan to reduce obesity in their community that is based on the assessment of their community’s environment for 4‐year‐old children.Community coalitions will identify and implement at least one local or institutional policy, system or environmental change that will improve nutrition and one that will increase physical activity for 4‐year‐old children.The project team will assess the perceived value that the community coalition members place on the effectiveness of the menu of evidence‐based or evidence informed educational programs and protocols in improving the environment that sustains healthy eating and promotes physical activity for 4‐year‐old children.The project team will test the main hypothesis that Community Coaching will enhance the capacity of the community in preventing childhood obesity by addressing the needs identified in the assessment and by providing the community coalitions in the intervention community (one per state) with Community Coaches training.

To summarize, existing community health coalitions will assess their environment using an ecological model of childhood overweight and then select evidence-based or evidence-informed approaches to implement over four years to address their community needs. This research will examine the effectiveness of a community coaching model on the ability of a community coalition to address the needs identified to improving the healthy eating and physical activity environment for 4‐year‐old children.

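### One community of each within-state pair is randomised to coaching, but the stated test and power statement name no state or pair term; if changes are correlated within states, a two-group test is conservative and loses power

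*Protocol article*

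**What the plan says.** **Design.** The objectives in the Background set out 14 communities, "two per state, one as an intervention community and one as a comparison community". Under Study design, "Similar-size intervention and comparison communities will be selected from each state". After screening, "communities will be randomly assigned to the intervention or comparison group", and "Each state will have one intervention and one comparison community". The same section opens by describing the work as done "Using a quasi-experimental design".

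**Power.** Study design claims 95% power for d of at least 0.8, two-tailed alpha .05, for intervention against comparison communities from pre to post, "using the community as the main unit of measure and community level variables as the main outcomes". It gives no correlation, either between pre and post or between the communities of one state.

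**Analysis.** Under Statistical analysis, "repeated measures ANOVA or corresponding non-parametric tests will be conducted to detect changes between intervention and comparison communities", before and after the four-year intervention, with significance at P < .05. Neither the analysis text nor the power text mentions state, pair or block.

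**The concern.** Similar-size communities chosen in pairs within a state, with one of each pair randomised, form a pair-matched cluster-randomised design with seven pairs. The natural error term is the variation among the seven within-state differences. A repeated measures ANOVA with only group and time uses the variation among communities within each arm instead.

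A stable difference between states cancels when change is analysed. A change common to both communities of a state does not: it cancels from the arm difference but stays in the two-group error term. The standard error is then too large, the test falls below its stated level, and power is lost. With only 14 units there is little power to spare.

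The design label matters too. Within-state randomisation is what justifies an exact within-pair test, and the article states random assignment while calling the study quasi-experimental.

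**Working it through.** **Inputs from the article (Study design, Statistical analysis):** 7 states with 2 communities each, one per arm; community as unit; two-tailed alpha .05; d = 0.8; pre-to-post contrast between arms.

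**Assumptions:** d is on the scale of the SD of community change (the article does not define the scale), changes are normal with SD 1, and the correlation ρ between the two changes within a state ranges from 0 to 0.5.

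**Step 1: the plan's own figure.** For 7 against 7 with d = 0.8, the noncentrality is 0.8 × √(7/2) = 1.497 on 12 df, critical value 2.179. Power is 28%, not 95%. The stated power needs a further assumption. If d is the difference in change over the raw SD, a pre-post correlation of about 0.93 is needed: 0.8/√(2 × (1 − 0.93)) ≈ 2.1, the effect size that gives 95% at 7 per arm. If d = 0.8 is entered as f = 0.4 for the interaction, about 0.71 is needed. That is a separate fault; here it only sets the starting level of power.

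**Step 2: the two tests.** With two time points, the group-by-time F of a two-group ANOVA equals the squared unpaired t on change.

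- Unpaired: t = (mean change coached − mean change uncoached) / √((s₁² + s₂²)/7), 12 df, critical value 2.179.
- Paired: t = mean of the seven within-state differences / (s_D/√7), 6 df, critical value 2.447.

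The true variance of the arm difference is 2(1 − ρ)/7. The unpaired test estimates 2/7, too large by the factor 1/(1 − ρ): 1.43 at ρ = 0.3 and 2 at ρ = 0.5. The paired test estimates the right quantity at any ρ; its noncentrality is 0.8 × √7 / √(2(1 − ρ)), that is 1.497, 1.789 and 2.117 at ρ = 0, 0.3 and 0.5.

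**Step 3: true size and power at d = 0.8** (unpaired by simulation, at least 400,000 trials per setting; paired power from the noncentral t).

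| ρ (assumed) | Unpaired size | Unpaired power | Paired size | Paired power |
|---|---|---|---|---|
| 0 | 5.0% | 28% | 5.0% | 24% |
| 0.1 | 4.1% | 27% | 5.0% | 27% |
| 0.2 | 3.2% | 26% | 5.0% | 29% |
| 0.3 | 2.4% | 25% | 5.0% | 33% |
| 0.5 | 1.1% | 23% | 5.0% | 43% |

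The powers cross between ρ = 0.10 (27.2% unpaired, 26.5% paired) and ρ = 0.15 (26.8% and 27.8%). Only a negative ρ would inflate false positives (unpaired size 8.2% at ρ = −0.3).

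**Step 4: non-parametric versions.** Mann-Whitney on change is the two-group counterpart; signed-rank on the seven differences is the paired one.

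| ρ | Mann-Whitney size / power | Signed-rank size / power |
|---|---|---|
| 0 | 3.8% / 23% | 4.6% / 23% |
| 0.3 | 1.9% / 20% | 4.9% / 30% |
| 0.5 | 0.9% / 18% | 4.7% / 40% |

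**Step 5: reach of the exact paired test.** Seven pairs give 2⁷ = 128 assignments, so the smallest two-sided p is 2/128 = 0.016. With six pairs it is 2/64 = 0.031. With five it is 2/32 = 0.0625, and .05 cannot be reached.

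**The case against.** **Silence in a condensed article.** A repeated measures ANOVA can carry state as a block, and a fuller plan may do so. A reader might infer that the pairs will be ignored; the article does not say that. What it does show is that the analysis text and the power text both describe the two-arm contrast, and neither refers to the pairing.

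**Correlation not documented.** A reader might also infer that the .05 test must be mis-sized. It need not be: at ρ = 0 its size is exact, and at positive ρ it errs towards caution and creates no false benefit of coaching. The evidence for positive ρ is mixed. Each state's co-investigator and graduate student follow the project (Qualitative data), and one state team maps both coalitions (Ripple effect mapping). But CHLI is completed within each community's coalition, CSAS is answered by each coalition's own members, and the Discussion concedes that identical communities could not be found within states. Below ρ of about 0.1 to 0.15 the paired t has less power. This stands, and it limits the size of the concern.

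**The fallback.** It would be wrong to say that no rank test corresponds to the planned contrast. With two time points, Mann-Whitney on change compares the arms properly; its weakness is only that it omits the pairs.

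**Fragility of pairs.** If one community is lost, a paired analysis loses its partner as well. That is a real cost.

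**Conclusion.** The concern holds as a mismatch between a design randomised within states and stated analysis and power texts that name no state or pair term. Its size is conditional. If changes are positively correlated within states, a two-group test is conservative and can lose power: 8 points at ρ = 0.3 (25% against 33%) and 20 points at ρ = 0.5 (23% against 43%). If they are uncorrelated, the two-group test is correctly sized and pairing costs about 4 points (28% to 24%). These figures assume d = 0.8 on the change scale, normal changes and equal variances.

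The reason to prefer the paired analysis is that it holds the .05 level at every correlation and follows from how communities were assigned. It is worth making, but it does not rescue the power claim: over this range neither test exceeds 43%. The design label is a smaller point, one of consistency.

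**What to change.** - For the community-level outcomes, define the primary comparison as the mean of the seven within-state differences (coached minus uncoached) in pre-to-post change, with a t test on 6 df and a 95% CI. ANOVA on change with state as a block is equivalent. If a fuller plan already includes state, say so in the analysis text.
- Name the non-parametric version: the within-state sign-flip test over 128 assignments, or the signed-rank test.
- Restate power for that analysis, giving the effect scale and the assumed correlations.
- State how an incomplete pair will be handled.
- Either describe the design as pair-matched and cluster-randomised, or list any state in which assignment was not random.

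The cost is wording, and Study status says that analysis of the main outcomes is only about to begin. The statistical price is a few points of power if state-level change is uncorrelated, and the loss of a whole pair when a community drops out; with only five complete pairs the exact test cannot reach .05.

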## Discussion

As a result of the study, a comprehensive childhood obesity prevention *Best Practices Tool Kit* will be developed to assist low‐income rural communities to 1) assess the environments of their communities as they relate to childhood obesity prevention and 2) learn to use community coaching techniques to help communities assess their strengths, strategize, and implement interventions to prevent childhood obesity.

Strengths of the study include the involvement of seven U.S. states in a new model (community capacity development using community coaching) of Extension intervention to prevent childhood obesity; a rural community setting; use of an ecological model of childhood overweight to focus on the environment of low‐income, 4‐year‐old children; and involvement of a community coalition to identify their own needs and implement corresponding intervention activities. Having communities choose their own interventions may increase the likelihood of sustainability once the project is complete. Limitations of the study include the inability to control for external factors which may contribute to or deflect from the development of community networks and collaborative local action around the issue of childhood obesity prevention; inability to identify identical communities within each state for comparison purposes and the relatively short time frame in which to measure and expect environmental and policy changes. Lessons learned from this integrated, community-based study will demonstrate an innovative way that Extension can work within communities to drive change especially given the emphasis on Health Extension as the next frontier.

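### For outcomes scored only at Year 2 and Year 5, the planned repeated measures ANOVA is a raw change-score test; adjusting the Year 5 community score for Year 2 is likely, but not certain, to be more precise

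*Protocol article*

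**What the plan says.** The Statistical analysis section assigns the main objective (objective 7, community capacity) to CHLI, Active Where? and CSAS. It names repeated measures ANOVA or corresponding non-parametric tests "to detect changes between intervention and comparison communities before and after the four year intervention", at P < .05. No baseline-adjusted model is mentioned.

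Study design fixes the comparison as "from pre to post using the community as the main unit of measure and community level variables as the main outcomes". It says "communities will be randomly assigned to the intervention or comparison group" and "Each state will have one intervention and one comparison community", which gives seven communities per arm.

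Table 2 ("Summary and timeline of outcome measures for intervention and comparison communities") shows CHLI and Active Where? at Year 2 (PRE) and Year 5 (POST) only. CSAS is collected in Years 2, 3, 4 and 5. Under the Active where? heading, about 30 parents per community are interviewed, and each completes the survey once.

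**The concern.** With two time points, the group-by-time term of a repeated measures ANOVA compares mean change between arms. That subtracts the whole baseline score, as if a community one unit higher at Year 2 were expected to be one unit higher at Year 5. If the correlation between waves is only moderate, full subtraction adds the baseline's noise to the estimate. A chance gap between arms at Year 2 is then over-corrected.

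ANCOVA estimates the slope instead of fixing it. The baseline is already being collected and arms are randomly assigned, so the adjustment is unbiased and needs no new data. What is at stake is the width of the confidence interval for the coaching effect in a trial with only 14 units.

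**Working it through.** **Inputs.** From the article: n = 7 communities per arm (N = 14), d = 0.8, two-sided alpha 0.05, the community as unit, and waves at Years 2 and 5. Assumed: r, the correlation between a community's Year 2 and Year 5 scores, shown over a range; and equal SD (σ) at both waves, with d measured on that SD.

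**The plan's own figure.** Study design states that 14 communities "will be sufficient to detect large effect sizes (d ≥ 0.8) with 95 % power for a two-tailed test at alpha = .05". This does not reproduce. A two-sample t test with 7 per arm has noncentrality 0.8 × √(7/2) = 1.497 on 12 df, and power 28.1%. A change-score test reaches 95% at this effect only if r is about 0.93. That is a separate problem; it is noted here because it sets the level from which any gain starts.

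**Identity.** On a simulated 14-community, two-wave dataset, the group-by-time F was 0.1547 and the squared t on change scores was 0.1547. They are the same test.

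**Variances of the estimated effect, 7 versus 7.**
- Change score: (2/n) × 2σ²(1 − r), on 12 df.
- ANCOVA: (2/n) × σ²(1 − r²) × [1 + 1/(N − 4)], on 11 df. The bracket is 1 + 1/10 = 1.10, the price of estimating the slope from 14 units.
- Ratio, ANCOVA to change: 1.10 × (1 + r)/2. It equals 1 at r = 2/1.10 − 1 = 0.82.

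Simulation with 100,000 trials per value of r and a true effect of 0.8 SD:

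| r | Ratio by formula | Ratio simulated | Power, change | Power, ANCOVA | CI width, ANCOVA/change |
|---|---|---|---|---|---|
| 0.3 | 0.715 | 0.715 | 21.6% | 28.1% | 0.851 |
| 0.5 | 0.825 | 0.823 | 28.0% | 32.8% | 0.914 |
| 0.7 | 0.935 | 0.938 | 42.9% | 45.3% | 0.972 |
| 0.8 | 0.990 | 0.989 | 58.5% | 58.5% | 1.001 |
| 0.9 | 1.045 | 1.048 | 86.6% | 84.6% | 1.029 |

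**State pairs also modelled.** Here the seven within-state Year 5 differences are regressed on the seven Year 2 differences. The slope now costs a factor 1 + 1/(7 − 3) = 1.25, and df fall from 6 to 5. The ratio is 1.25 × (1 + r)/2, which equals 1 at r = 0.6. Simulated with no state effect:

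| r | Ratio simulated | Power, change | Power, ANCOVA | CI width, ANCOVA/change |
|---|---|---|---|---|
| 0.3 | 0.813 | 18.7% | 21.9% | 0.928 |
| 0.5 | 0.928 | 24.7% | 25.6% | 0.997 |
| 0.6 | 1.000 | 29.2% | 29.1% | 1.030 |
| 0.7 | 1.057 | 37.1% | 35.2% | 1.061 |

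Interval width breaks even at r of about 0.5, variance at about 0.6.

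**Is moderate r plausible?** For Active Where? the covariate is a mean of 30 parents. If the two waves sample different parents, sampling noise alone caps r at the reliability of that mean, 30ρ/(1 + 29ρ), where ρ is the intracluster correlation. For assumed ρ of 0.02, 0.05 and 0.10 this is 0.6/1.58 = 0.38, 1.5/2.45 = 0.61 and 3/3.9 = 0.77. For CHLI the documents offer nothing comparable.

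**The case against.** Repeated measures ANOVA is a standard, valid analysis. The article is a condensed account, and covariates are often settled in a fuller plan. The sign of the gain depends on an r that the documents do not give. All of that is true. But the article does name the model for its main objective, so the choice can be judged as written.

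Three stronger readings are tempting and are not supported.

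- **That baseline adjustment always wins when r < 1.** The large-sample ratio (1 + r)/2 suggests variance reductions of 35%, 25% and 15% at r = 0.3, 0.5 and 0.7. With 14 communities they are about 28%, 18% and 6%, and the advantage is gone near r = 0.8.
- **That the authors concede baseline imbalance.** The Discussion lists "inability to identify identical communities within each state for comparison purposes". That concerns imperfect matching of communities; it does not say that the arms differ on CHLI, CSAS or Active Where? scores at Year 2.
- **That change scores bias the coaching effect.** Under random assignment the change-score estimate is unbiased over allocations. Regression to the mean enters as chance variance in a given allocation.

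The identity also has limits. It does not hold for CSAS if all four annual waves enter the model, nor for the non-parametric option.

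**Conclusion.** The point holds as a modest, low-cost improvement for two-wave outcomes analysed at community level. With arms compared unpaired, ANCOVA gains about 6 to 7 points of power at r = 0.3, 5 at r = 0.5 and 2 at r = 0.7. It gains nothing near 0.8 and loses about 2 points at 0.9. With state pairs modelled, it helps only below r of about 0.5 to 0.6. These figures rest on an assumed r, equal SDs at the two waves, normal scores and, for the paired figures, no state effect.

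The planned analysis is not invalid. Even with the gain, power for 0.8 SD at moderate r stays far below the 95% in Study design.

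**What to change.** In Statistical analysis, for CHLI, Active Where? community means and any CSAS comparison limited to Years 2 and 5, make the primary model the Year 5 community-level score on arm, with the Year 2 community-level score as covariate and arm kept in the model. Keep the change-score result as a sensitivity analysis. Say whether state pairs are modelled, since that moves the break-even point. Make the choice before looking at outcomes by arm; the article's Study status section says analysis of the main outcomes is only beginning.

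A shortcut that saves the pairs' degrees of freedom should not be used for the effect estimate: regressing Year 5 on Year 2 without arm and then comparing residuals between arms. It shrinks the effect by the share of baseline variance explained by arm, which averages 1/13 under randomisation: 0.80 × 12/13 = 0.74. In simulation the mean estimate was 0.74, and 0.59 when arms differed by more than 0.8 SD at baseline.

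The cost is a change of analysis wording, one degree of freedom and about 10% variance inflation from estimating the slope (about 25% if pairs are modelled). No extra data are needed.
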